### Qualitative Outcome Measures

To understand the carer and patient experience and perception of the value of the FREER intervention, the first 10 participant pairs (both patient and carer, total n=20) who consent to be interviewed will participate in 30 to 60 minute semistructured interviews. Participants will be invited to participate in the interviews up to 2 weeks post T3 (Table 1) via telephone. The first interview with the patient and carer, who will be interviewed together if possible, will be an open discussion focused on topics identified in the literature and will be used to develop the semistructured interview schedule for the remaining interviews. The interviews will be recorded and analyzed qualitatively, using thematic analysis of verbatim interview transcripts based on the principals of grounded theory. For independence, the interviews will not be performed by nor in the presence of the study dietitian who implemented the FREER pilot intervention, and the interviews will be conducted and reported according to the Qualitative Research Review Guidelines (RATS) [33].

### Process Evaluation

A quantitative process evaluation will be simultaneously implemented. The intervention fidelity, intervention adaptions, and attrition rate will be recorded through researcher logs and voice-recorded telehealth consultations. Resources used to implement the process evaluation are outlined in Multimedia Appendix II.

### Adverse Events

As the patients are recognized to have acute or chronic morbidity requiring an inpatient admission, as well as being diagnosed with PEM at baseline, medical events and continued PEM are likely to be frequent as reflecting this medical and nutritional status. The FREER nutrition intervention reflects the current usual and best dietetic practice where only the method of engagement with patients and family carers is modified. Although nutritional treatment for PEM is considered low-risk adverse events may occur.

Adverse events possibly or directly related to FREER intervention methods will be recorded. These may be related to (1) nutrition-related biochemistry, (2) bowel habits, (3) allergic reactions to recommended foods and beverages, or (4) hydration status but will only be considered adverse events if status worsens from baseline. These intervention-related adverse events will be considered serious if they lead to the transfer from rehabilitation to acute care, additional intervention by the rehabilitation physician, or mortality.

### Ethical Considerations and Withdrawals

This study was approved by the North Coast New South Wales Human Research Ethics Committee (Approval HREC/18/NCC/47) and Governance (528N), as well as the Bond University Human Research Ethics Committee (528N-HREC/18/NCC/47). Written informed consent will be required for patients and family carers prior to their participation. Withdrawal of the patient or the carer from the study will cease the FREER intervention being delivered to both members of the caring pairs. However, the nonwithdrawing patient will continue to be asked to participate in outcome assessments if the carer withdraws from the study.

### Statistical Analysis

Intention-to-treat analysis will be used to evaluate quantitative outcome measures. However, those discharged home and those discharged to aged care will be reported separately. If the intervention group sample size is substantially smaller than the historical control group, cases will be matched to create a 1:1 ratio of control versus intervention. Outcomes and participant characteristics will be summarized via descriptive statistics. Changes in the control group over time have been previously analyzed and published [10]; however, the intervention group will be analyzed for change over time in continuous variables using linear mixed models, and chi-square tests for changes over time in categorical variables.

To determine the difference in primary and secondary outcomes between the intervention and control group over time, both continuous and categorical outcome variables will be analyzed via a marginal model using generalized estimating equations, with study group allocation and time in months as main predictors, and adjusting for baseline outcome measures.

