Interventions to improve the nutritional status of older adults and the integration of formal and family care systems are critical research areas of the United Nations (items 2.6.10 and 2.10.7) [9], and implementing these approaches in rehabilitation facilities is of primary importance in Australia. Australian rehabilitation units have the highest prevalence of PEM internationally (45%-65% versus 30%-45% in the United States, Europe, and Asia when using the same diagnostic tool, N=17 studies, N=4591 participants) [10]. Although the goal of rehabilitation is to increase independence, observational research identified that older patients admitted to rehabilitation with PEM and receiving usual care were being discharged to the community with PEM, where they remained malnourished for at least 12 weeks in their own homes [10]. A recent meta-analysis found the prevalence of PEM in older Australians living in their own homes is 6% (95% CI, 4.4%-8.2%), which represents 228,000 malnourished older adults in 2017 [11]. Further downstream health consequences are severe, where PEM significantly predicts decreased physical function, institutionalization, and rehospitalization, poor quality of life, and death [3,10,12].

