### Quantitative Outcome Measures

The selected quantitative outcome measures have been validated and previously piloted in the target population [10,12], and are outlined in Table 1. Nutritional status as defined by the PG-SGA numerical score [26] is the primary outcome (increasing score indicates increasing severity of PEM with typical scores 0-30). The PG-SGA was chosen in preference to the Mini Nutritional Assessment [27] and other nutrition assessment tools as both its score and categorization have the strongest criterion validity in this population and it has shown sensitivity to change in 1 week [1]. Secondary outcomes for the patient include (1) additional measures of nutritional status (PG-SGA rating of A, B or C), (2) energy and protein intake (kJ and grams per day), (3) mid-arm circumference (MAC), (4) physical function by Modified Barthel Index (MBI) [28], (5) Functional Independence Measure (FIM) [29], (6) body weight (kg), (7) health-related quality of life using a generic preference-based instrument (AQoL-6D) [30], (8) rehabilitation length of stay, (9) patient nutrition service satisfaction as per purpose developed Nutrition Service Satisfaction Survey modified from the Patient Satisfaction Survey with Inpatient Clinical Nutrition Services (Multimedia Appendix 2) [31], (10) 3 month rehospitalization (yes or no; and length of stay), (11) aged care admission (yes or no; and level of care). Secondary outcomes of the family carer are carer burden (Zarit Burden Interview Score [32]) and carer nutrition service satisfaction (Carer Nutrition Service Satisfaction Survey modified from the Patient Satisfaction Survey with Inpatient Clinical Nutrition Services and shown in Multimedia Appendix II) [31]. All assessment tools and physical measures for the patient will be completed by the study dietitian during patient interview, excepting the service satisfaction questionnaire which will be completed by the patient. All assessment tools for the family carer will be self-completed unless via telephone interview, or the carer has limitations with reading or writing.

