The primary and secondary outcomes will be measured at baseline (recruitment T1), rehabilitation discharge (T2), and 12-weeks postdischarge (T3), as described in Table 1. Outcomes will be assessed at the rehabilitation site (T1 and T2) and a home visit or medical records as relevant (T3). If the participant is not able to be assessed at discharge at the rehabilitation site, T2 outcomes will be informed via telephone interview and medical records wherever possible; however, the physical measures including a component of the PG-SGA and the MAC would not be performed in this instance.

**Table 1 table1:** FREER pilot study primary and secondary outcomes, assessment methods, and timepoints.

Outcome	Baseline (T1)	Discharge (T2)	Postdischarge (T3)	Measure and source of data
Nutritional status	X	X^a^	X	PG-SGA^b^ score and category Patient and carer interview
Weight (kg)	X	X	X	Calibrated study scales or medical records Patient interview
Energy intake (kJ)	X	X	X	24hr dietary recall Patient and carer interview
Protein intake (g)	X	X	X	24hr dietary recall Patient and carer interview
Mid-arm circumference	X	X	X	Tape measure Patient interview
Physical function	X	X	X	Modified Barthel Index Patient and carer interview supported by allied health care team Medical records
Physical function	X			Functional Independence Measure Medical records
Health-related quality of life	X	X^a^	X	AqoL-6D^c^ Patient interview
Patient nutrition satisfaction			X	Patient Satisfaction Survey Self or carer-completed
Rehabilitation length of stay		X		Medical records
Rehospitalization and length of stay			X	Medical records
Residential aged care admission			X	Medical records Patient or carer report
Carer burden		X	X	Zarit Burden Interview Self-completed
Carer nutrition satisfaction			X	Carer Satisfaction Survey Self-completed
Patient and carer experiences and perceptions of value^d^			X^e^	Qualitative interview conducted via telephone

^a^If T1 and T2 occur 6 days or less apart this measure will not be repeated as it will have assumed not to have significantly changed within that short time period as per feasibility data [10].

^b^PG-SGA: Patient Generated Subjective Global Assessment.

^c^AQoL-6D: Assessment of Quality of Life-6D.

^d^A subgroup of participants will be invited to participate by consecutive sampling with a target sample size of n=10 carers and n=10 patients.

^e^The interviews will be conducted up to 2 weeks following T3 by an independent researcher.

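### Length of stay, rehospitalization and aged care admission have no baseline value, so the plan's only adjustment drops out of these historically controlled comparisons although the T1 PG-SGA score is available

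*Protocol article*

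**What the plan says.** The between-group analysis is set out in one sentence of the protocol's Statistical Analysis section. It opens "To determine the difference in primary and secondary outcomes between the intervention and control group over time, both continuous and categorical outcome variables will be" analysed with a marginal model by generalized estimating equations, "with study group allocation and time in months as main predictors, and adjusting for baseline outcome measures". No other covariate is named. The same section provides 1:1 matching, but only if the intervention group turns out substantially smaller than the control group, and it names no matching variables.

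The Quantitative Outcome Measures section lists among the patient secondary outcomes "10) 3 month rehospitalization (yes or no; and length of stay), (11) aged care admission (yes or no; and level of care", together with rehabilitation length of stay. In Table 1 the rows "Rehospitalization and length of stay" and "Residential aged care admission" are marked at T3 only, and "Rehabilitation length of stay" at T2 only. "Patient nutrition satisfaction" is also marked at T3 only. PG-SGA score and category are marked at T1, T2 and T3.

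**The concern.** Adjustment for baseline is the only statistical protection the plan gives the between-group contrasts. The groups are not randomised: controls come from a 2013-2014 cohort at two units (14 and 16 patients), of which one is the FREER site. The Discussion concedes selection bias but offers no analytic remedy.

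For an outcome with no T1 value the adjustment term does not exist, and with one scheduled record there is essentially no time trend to estimate. Any difference between the groups in malnutrition severity at entry that is prognostic for admission or length of stay then passes straight into the estimated FREER effect, or masks one. Hospital and aged care admission rates are named in aim 1 as comparisons with usual care, and the pilot is meant to supply preliminary efficacy data for a later trial. A biased estimate would be carried forward into that planning.

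**Working it through.** **1. Model terms against the measurement schedule.** Inputs: the predictor list in Statistical Analysis and the columns of Table 1.

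| Outcome | T1 | T2 | T3 | Own baseline exists? | Time term estimable? |
|---|---|---|---|---|---|
| PG-SGA score (primary) | yes | yes | yes | yes | yes |
| Rehabilitation length of stay | no | yes | no | no | no |
| Rehospitalization and its length of stay | no | no | yes | no | no |
| Aged care admission | no | no | yes | no | no |
| Patient nutrition satisfaction | no | no | yes | no | no |

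For the last four rows, group + time + own baseline reduces to group alone.

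**2. Is a usable covariate at hand?** PG-SGA diagnosis is an entry criterion, controls are said to have met the same criteria, and the primary analysis already needs the T1 score in both groups. No new data are required.

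**3. Possible size.** The sample size was set by resources, so there is no power calculation to reproduce. The documents give no event rates, prognostic slope or baseline gap, so every value here except n is an assumption.

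Setup: 30 v 30; logit P(event) = -0.6 + ln(OR) × z, where z is T1 PG-SGA in SD units; no group effect; FREER mean lower by the gap d. Averaging over z gives the two crude risks. The crude odds ratio is [p1/(1-p1)] / [p0/(1-p0)]. For OR 2 and d = 0.5, p0 = 0.368 and p1 = 0.298, so (0.298/0.702) / (0.368/0.632) = 0.73. Rejection rates come from 6,000 simulated trials per setting (Wald test, two-sided 5%; Monte Carlo standard error about 0.3 points).

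| OR per SD | Gap (SD) | Risk, control v FREER | Crude odds ratio (truth 1) | Type I error, crude | Type I error, adjusted for T1 PG-SGA |
|---|---|---|---|---|---|
| 1.5 | 0.3 | 36% v 33% | 0.89 | 4.9% | 4.7% |
| 1.5 | 0.5 | 36% v 32% | 0.82 | 6.3% | 4.9% |
| 2 | 0.3 | 37% v 33% | 0.83 | 5.3% | 4.5% |
| 2 | 0.5 | 37% v 30% | 0.73 | 7.7% | 4.8% |
| 2.5 | 0.3 | 38% v 32% | 0.79 | 6.1% | 4.6% |
| 2.5 | 0.5 | 38% v 29% | 0.68 | 10.0% | 4.4% |

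Each setting has about 20 to 21 events in total. The error rate moves clearly only with a strong slope and a large gap. The crude odds ratio is off target in every row, though modestly in the milder ones.

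**The case against.** Four points deserve weight.

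- **The wording is plural.** Baseline outcome measures could mean the baseline values of several outcomes, PG-SGA included, entered in every model. That reading is possible, but the text does not say so. The usual meaning is each outcome's own baseline, and one sentence would settle it.
- **The article is condensed.** The sentence cannot be literal for every secondary outcome, since the carer outcomes have no control data at all. Still, the article states the model and its covariates, and its own Table 1 shows that they cannot apply to these rows. This is a stated choice that does not fit, not just omitted detail.
- **The prognostic evidence is indirect.** The Background says "PEM significantly predicts decreased physical function, institutionalization, and rehospitalization, poor quality of life, and death". A reader might infer that the document thereby shows that PG-SGA severity drives all these outcomes in this sample. It does not. Every FREER patient and every control has PEM, the sentence says nothing about score severity among patients rated B or C, and it names neither rehabilitation length of stay nor satisfaction. This objection stands: the prognostic slope is an assumption.
- **The consequence is limited.** These are secondary outcomes in a pilot that concedes selection bias and defers to a later trial. That stands too, and it limits how much weight the point can bear.

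The conditional matching does not answer the concern. It serves to equalise numbers, names no variables, and would not be triggered if 30 patients are recruited.

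**Conclusion.** The point holds for rehabilitation length of stay, rehospitalization and aged care admission. On the ordinary reading of the plan, their comparison with the historical controls is unadjusted, while a sensible T1 covariate is already collected. The primary outcome is not affected.

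The benefit of adjusting cannot be sized from the documents. Under the assumed values, crude type I error is about 7% to 10% at a 0.5 SD gap with odds ratio 2 to 2.5, against 4% to 5% adjusted. At a 0.3 SD gap with odds ratio 1.5 to 2 there is little or no inflation.

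Two stronger readings are not supported. A reader might infer a definite power gain for length of stay, but the documents give neither an effect size nor a correlation with PG-SGA, and a baseline gap would itself erode such a gain. A reader might also count patient satisfaction as a fourth affected contrast. Aim 1 does list it, but the documents do not show that the controls completed the survey, so the contrast may not be estimable at all.

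This is a cheap improvement to the covariate choice and not a flaw that undermines the pilot.

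**What to change.** Add a sentence to Statistical Analysis: for rehabilitation length of stay, rehospitalization and aged care admission, the between-group model uses one record per patient, has no time term and adjusts for T1 PG-SGA score, with penalised logistic regression where admissions are few; the crude contrast is reported beside the adjusted one. Treat patient satisfaction the same way only if the controls completed the survey. For the remaining outcomes, say that the baseline covariate is the outcome's own T1 value.

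The cost is one extra parameter in models that may have about 20 events, or fewer after attrition, and an adjusted odds ratio that is conditional and so on a different scale from the crude one. A routine second covariate such as the Modified Barthel Index would be fragile at that event count. No new data are needed. Adjustment for PG-SGA leaves the differences in calendar period and site in place, and the report should say so.

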## Results

Recruitment for the FREER pilot study began July 4, 2018, and is ongoing. At the time of manuscript submission, 14 participant pairs have been identified as eligible, with nine pairs (n=18 participants in total) consenting (preliminary recruitment rate is 9/14, 64%). The reasons for nonparticipation were family carer not interested (3/5, 60%) and patient not interested (2/5, 40%). Three family carers have withdrawn from the study at T2 (discharge). The stated reasons for withdrawal were (1) family carer being overwhelmed with caring duties (1/9, 11%), (2) family carer being overwhelmed with caring duties in the context of worsening carer health (1/9, 11%), and (3) changes to the family caring structure (1/9, 11%). Three of 9 (33%) patients were withdrawn following T2 because of (1) death due to the complication of a preexisting condition (2/3; 67%), and (2) geographical relocation out of the study area (1/3; 33%). The preliminary carer attrition rate is 33% (3/9) and the patient attrition rate is 33% (3/9).

## Discussion

Although compared with usual care, supportive nutrition interventions to increase dietary protein and energy intake in malnourished patients across all settings decrease all-cause mortality (risk ratio .78, 95% CI: 0.66-0.92, N=12 trials, N=6683 participants), the evidence is biased by poor quality study designs with limited translation of effective models of care to the clinical setting [2]. The pragmatic design of the FREER intervention will support translation to practice. Although the current pilot study has limitations related to study design, including the use of a historical control group causing selection bias and a lack of blinding, it will provide sufficient preliminary feasibility and efficacy data to inform the development of a future adequately powered, and well-designed RCT. In addition to the need for high-quality RCTs which evaluate nutrition interventions for malnourished older adults, research engaging family carers as part of the medical and nutritional care team is in demand [34,35]. By using a relevant framework [22] this research is designed to inform health service policies and will provide the foundations of future interventions translated into other health care settings and rehabilitation units.

## Appendix

Multimedia Appendix 1 The FREER intervention strategies.

Multimedia Appendix 2 FREER intervention and research materials.

## Abbreviations

AQoL-6D: Assessment of Quality of Life-6D
FREER: Family in Rehabilitation: EmpowERing Carers for improved nutrition outcomes
MAC: mid-arm circumference
PEM: protein-energy malnutrition
PG-SGA: Patient Generated Subjective Global Assessment
RCT: randomized controlled trial
